### Methods in analysis to handle protocol non-adherence and any statistical methods to handle missing data {20c}

The results will be analyzed according to the following principles: the “intention-to-treat” (all randomized participants, irrespective of protocol adherence), the “per protocol” (only participants that were treated according to the protocol), and the “as treated” (all participants according to the treatment they received) principles. These three analyses will be compared to show how a lack of data possibly impacts the results. For the primary endpoint, no missing data are expected. For secondary endpoints (cost-effectiveness evaluation), the predictive mean of the other values within the arm will be used.

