### Criteria for discontinuing or modifying interventions {11b}

After allocation to the experimental or control arm, several circumstances—specified as perioperative exclusion criteria- can still lead to excluding the patient from the study. A patient allocated to the control arm may be excluded in case of a clear indication for a hypersensitivity reaction to commercially available fibrin sealants. Patients allocated to L-PRF treatment may be excluded if the L-PRF preparation process fails or if the product is considered of insufficient quality. In case the surgeon identifies other intraoperative findings that may constrain the conduct of the study procedure the subject can be excluded as well, to ensure optimal patient care in that situation. For example, when the damage to the dura is exceptional, the surgeon may opt for a multilayer reconstruction using multiple grafts, commercially available sealants, and autologous materials. Furthermore, study participants can withdraw from the study at any moment, implying that all subsequent study procedures and data collection are discontinued.

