### Sample size {14}

Sample size calculation was performed according to the primary outcome, using an online power calculator for binary outcome non-inferiority trials (Sealed Envelope Ltd. Available from: https://www.sealedenvelope.com). This is a non-inferiority trial with a binary outcome using a one-sided alpha 0.05 and 80% power. The assumed success rate is 94.3% in the control arm, based on center-specific experience as well as the literature [14]. Data on the use of L-PRF for this indication is limited, but we assume a 95% success rate based on prior feasibility studies [8–10].

The statistical hypothesis for testing the treatment difference is presented as follows; H_0_: Δ ≤  − 0.07 tested against the alternative hypothesis H_A_: Δ >  − 0.07, where Δ is the difference between the success rates of experimental and control condition and − 0.07 is the non-inferiority difference. The non-inferiority limit was set at 0.07 considering (a) reported CSF leakage rates without commercially available fibrin sealant averaging 17.2% [15] and (b) important additional benefits of L-PRF compared to commercially available fibrin sealants including the completely autologous nature (eliminating immune reactions), presence of immunologic cells and reduced costs.

Based on this power calculation, 212 patients need to be included, 106 in each group. In order to account for potential missing follow-up information, failure of L-PRF preparation, or non-adherence to the allocation (expected drop-out rate less than 2%), 220 subjects will be enrolled, 110 in each group.

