### Plans to promote participant retention and complete follow-up {18b}

The postoperative follow-up visits are planned and notified to the patient before hospital discharge. If the patient is not present at one of these appointments, or if the clinical follow-up appointment is rescheduled outside the visit time window (+ / − 1 week for FU1 and FU2; + / − 2 weeks for FU3 and FU4), the patient is contacted by telephone to reschedule the visit. If this attempt is unsuccessful, the patient is considered lost to follow-up. In case of subject withdrawal, an exit note is added to the electronic Case Report Form (e-CRF) mentioning the withdrawal date and reason of withdrawal.

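### Comparing ITT, per-protocol and as-treated cannot show the effect of missing leak outcomes, and the statement that none are expected conflicts with other sections

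*Protocol article*

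**What the plan says.** All references are to the protocol article.

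- **Section {20c}, non-adherence and missing data.** Three analyses are planned: intention-to-treat (everyone randomized), per-protocol (those treated as the protocol requires) and as-treated (grouped by treatment received). Their stated purpose is: "These three analyses will be compared to show how a lack of data possibly impacts the results". The section adds: "For the primary endpoint, no missing data are expected". Its one imputation rule concerns secondary (cost-effectiveness) endpoints.
- **Sample size {14}.** The 212 patients needed become 220 enrolled, with this reason: "In order to account for potential missing follow-up information, failure of L-PRF preparation, or non-adherence to the allocation". Drop-out is put below 2%.
- **Participant retention {18b}.** A patient who misses a visit, or whose visit moves outside its window, is telephoned to rebook. Then: "If this attempt is unsuccessful, the patient is considered lost to follow-up". The rule covers every follow-up visit from 2 weeks onward.
- **Discontinuing or modifying interventions {11b}.** A participant may withdraw at any time, "implying that all subsequent study procedures and data collection are discontinued".
- **Outcomes {12}.** The primary endpoint is read at 3 months.

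**The concern.** The check named for missing data answers a different question. By the article's own definitions the three sets vary in who adhered and which treatment was given. A patient whose 3-month leak status is unknown has no outcome to contribute to any of them unless some rule supplies one. The three results could agree closely while all being affected by the same missing outcomes, and the stated purpose would lead a reader to take that agreement as reassurance.

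The expectation of complete primary data is also at odds with the rest of the article. The sample size section, which is built on the primary outcome, budgets for missing follow-up. The retention and withdrawal rules describe how a patient can leave follow-up before 3 months.

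What is at stake is bias rather than power. Only about five or six leaks per arm are expected, so a handful of unknown outcomes in the L-PRF arm could decide whether the lower limit clears -7 points.

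**Working it through.** **Inputs, all from Sample size {14}:** "one-sided alpha 0.05 and 80% power"; "The assumed success rate is 94.3% in the control arm"; for L-PRF, "we assume a 95% success rate based on prior feasibility studies"; margin 0.07; 106 per arm needed, 110 per arm enrolled. The 95% interval is the one named in Statistical methods {20a}.

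**1. Reproducing the plan's figure.**
n per arm = (z0.95 + z0.80)² × [pC(1 - pC) + pT(1 - pT)] / (pT - pC + 0.07)²
= (1.645 + 0.842)² × (0.05375 + 0.04750) / 0.077²
≈ 105.6, so 106 per arm and 212 in total. This matches.

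**2. Allowance.** 212 / 0.98 = 216.3, so 217 would cover a 2% loss. Enrolling 220 leaves 220 - 212 = 8 spare (8/220 = 3.6%), or 4 per arm. Computed power is 81.4% at 110 per arm and 80.1% at 106, so the allowance is adequate for power.

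**3. Assumed leak counts.** Control: 0.057 × 110 = 6.3, taken as 6. L-PRF: 0.05 × 110 = 5.5, taken as 5. Starting from 6 instead would bring each result below one patient nearer to failure.

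**4. Lower limit of the difference in success rates (L-PRF minus control).**
L = (pT - pC) - z × √[pT(1 - pT)/nT + pC(1 - pC)/nC], with z = 1.645 for the 90% interval (one-sided 0.05) and 1.960 for the 95% interval.

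Example, 8 v 6 leaks: pT = 102/110 = 0.9273 and pC = 104/110 = 0.9455, a difference of -0.0182. The standard error is √[(0.0674 + 0.0516)/110] = 0.0329. L at 90% = -0.0182 - 1.645 × 0.0329 = -0.0723.

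| Scenario | Leaks, L-PRF v control | 90% limit (points) | 95% limit (points) |
|---|---|---|---|
| Planned, nobody missing | 5/110 v 6/110 | -3.92 pass | -4.85 pass |
| 1 unknown L-PRF counted as leak | 6/110 v 6/110 | -5.04 pass | -6.00 pass |
| 2 unknown L-PRF counted as leaks | 7/110 v 6/110 | -6.14 pass | -7.14 fail |
| 3 unknown L-PRF counted as leaks | 8/110 v 6/110 | -7.23 fail | -8.26 fail |
| Same 3 dropped | 5/107 v 6/110 | -4.11 pass | -5.05 pass |
| 4 unknown L-PRF counted as leaks | 9/110 v 6/110 | -8.31 fail | -9.38 fail |
| 4 unknown in each arm, all leaks | 9/110 v 10/110 | -5.32 pass | -6.51 pass |

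In the rows that add L-PRF leaks, any unknown control patients count as leak-free. Newcombe limits change none of these results: at 90%, two adverse losses give -6.5 and three give -7.6.

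**5. What the planned comparison would reveal.** Take the three-patient case with adherent patients who received their allocated treatment. If unknown outcomes are left out, all three sets show 5/107 v 6/110 and agree at -4.1. The -7.2 does not appear in any of them.

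**The case against.** The strongest reply is that this is a condensed article and an analysis plan may exist. Which set decides non-inferiority, and what sensitivity analyses are run, commonly sit there. That stands: a reader might infer that missing outcomes will go untested, but the article alone cannot show it. What remains is that the check the article does state is the wrong one for its stated purpose.

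A reader might also infer a complete-case analysis. No section says so, and intention-to-treat is defined as everyone randomized. The point does not depend on it. If intention-to-treat filled in missing outcomes by some rule, its difference from per-protocol would mix that rule with adherence and still not isolate the effect of missing data.

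A further inference is that the most favourable of the three results could be picked. The article commits to comparing all three, so a split would be visible. Nor does anything make as-treated primary.

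Primary outcomes may also be harder to lose than the follow-up rules suggest. A leak that counts is one needing revision or another intervention, which would normally leave a hospital record. Sections {18a} and {22} draw on electronic files, only the 2-week visit is outside standard care, and digital follow-up has been allowed since March 2020. This lowers the likely number of unknowns and makes the remedy practical. The retention section does not, however, say that records will be searched before a patient is classed as lost. Stopping data collection at withdrawal is a consent position, not a statistical error. It matters here only because it conflicts with expecting complete data.

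**Conclusion.** The point holds in a limited form. The sentence on what the three-way comparison shows is wrong on the article's own definitions. The expectation of no missing primary data conflicts with {14}, {18b} and {11b}.

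On size, with 5 v 6 leaks among 110 per arm, three unknown L-PRF outcomes separate a pass (-4.1 when dropped) from a fail (-7.2 when counted as leaks) on the 90% interval.

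It would be tempting to say that the plan's own expected loss overturns the result. That is not supported. From the assumed 5 v 6, a 2% loss (two per arm) in its worst case still passes at 90% (-6.1), and fails only on the 95% interval (-7.1). Part of the allowance covers failed preparation and non-adherence, where leak status may still be known. The reversal also needs losses adverse to L-PRF: four leaking losses in each arm still pass (-5.3).

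The figures rest on leak counts rounded from the planned rates and on Wald limits. They show how sensitive the result is and do not predict how many outcomes will be missing.

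**What to change.** - Delete or correct the sentence in {20c} that gives the three-way comparison as evidence on missing data, and reconcile the statement that none are expected with {11b}, {14} and {18b}.
- In {18b}, do not class a patient as lost for the primary endpoint until 3-month leak status has been sought by telephone and from the hospital record. After withdrawal, do this only where consent allows.
- For patients still unknown, report a worst case (L-PRF missing counted as leak, control missing counted as no leak) and a tipping-point table across combinations of leaks among the unknowns in each arm.
- Label as-treated as supportive only. Which of intention-to-treat and per-protocol decides non-inferiority may be set in the analysis plan.

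The cost is some wording, a few telephone calls and one extra table.

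### Agreement between the ITT, per-protocol and as-treated results cannot show robustness to missing leak outcomes, and the plan's own rules allow such outcomes to be missing

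*Protocol article*

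**What the plan says.** All of this is in the protocol article.

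- **Section 20c (non-adherence and missing data)** states that "For the primary endpoint, no missing data are expected". It names three analyses: intention to treat (everyone randomised), per protocol (those treated as planned) and as treated (by product received). It adds: "These three analyses will be compared to show how a lack of data possibly impacts the results". A fill-in rule is given only for secondary endpoints, namely the cost-effectiveness evaluation.
- **Section 14 (sample size)** raises enrolment from 212 to 220. The first reason given is "In order to account for potential missing follow-up information". The other two are failed L-PRF preparation and non-adherence, and the pooled drop-out is put below 2%.
- **Section 11b (discontinuation)** lets patients withdraw at any time, "implying that all subsequent study procedures and data collection are discontinued".
- **Section 18b (retention)** describes a telephone call after a missed or badly timed visit: "If this attempt is unsuccessful, the patient is considered lost to follow-up".
- **Section 12 (outcomes)** places the primary endpoint at 3 months after surgery.

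**The concern.** There are two faults in the printed text.

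First, the expectation in section 20c sits badly with the other sections. Section 14 sizes the trial on the primary outcome and budgets for missing follow-up. Sections 11b and 18b describe two routes by which a patient's leak status at 3 months can become unknown.

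Second, the comparison in section 20c cannot do what it is said to do. It addresses departures from the allocated product, whereas missing outcomes are a different problem. If the text is followed, agreement between the three results would be reported as reassurance about missing data when it gives none. About 6 leaks per arm are expected against a 7-point margin, so a few unknown outcomes can matter if the result lies near the boundary.

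**Working it through.** **Inputs.** Section 14 specifies a design "using a one-sided alpha 0.05 and 80% power". For the comparator: "The assumed success rate is 94.3% in the control arm". For L-PRF: "we assume a 95% success rate based on prior feasibility studies". The margin is 0.07, with 106 evaluable and 110 enrolled per arm.

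**Step 1: reproduce the plan's sample size.**
n per arm = (z_0.95 + z_0.80)² × [0.95×0.05 + 0.943×0.057] / (0.007 + 0.07)²
= (1.645 + 0.842)² × 0.10125 / 0.005929 = 105.6, which rounds up to 106 per arm and 212 in total. This matches the article.

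**Step 2: how many outcomes could be missing on the plan's own figures.** 212 / 0.98 = 216.3, so 217 would cover a 2% loss, and 220 are enrolled. Two per cent of 110 is 2.2, so a rate below 2%, split evenly, means at most about 2 per arm. This is a ceiling for missing outcomes, because the allowance also covers failed preparation and non-adherence.

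**Step 3: what the three sets can detect.**

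| Patient | ITT | Per protocol | As treated |
|---|---|---|---|
| Followed, received the other product | counted as randomised | left out | counted by product received |
| Leak status at 3 months unknown | no observed outcome | no observed outcome | no observed outcome |

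The sets separate on the first row only. Whatever happened to patients in the second row, all three results stay the same unless a rule assigns them an outcome, and the article states none for this endpoint.

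**Step 4: an extreme bound.** Expected leaks in 110 are 110×0.05 = 5.5 (L-PRF) and 110×0.057 = 6.3 (control), so 6 per arm is a fair example. Write leaks as a/n (L-PRF) and b/m (control). The lower limit of the difference in success rates (L-PRF minus control) is

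(b/m − a/n) − 1.645 × √[(a/n)(1−a/n)/n + (b/m)(1−b/m)/m].

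This is the simple 90% two-sided interval, which matches a one-sided 5% test.

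- Observed, 6/108 vs 6/108: 0 − 1.645×0.03117 = −5.1 points. Non-inferior.
- One of the two missing L-PRF patients leaked, 7/110 vs 6/108: −0.81 − 1.645×3.206 = −6.1 points. Still non-inferior.
- Both leaked, 8/110 vs 6/108: −1.72 − 1.645×3.315 = −7.2 points. Not shown. Counting the two missing controls as leak-free (6/110) also gives −7.2.

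**Step 5: how often this would happen.** I summed exact binomial probabilities at leak rates of 5.0% and 5.7%, with 2 missing per arm and the same interval. The table gives the share of results passing on observed cases that would reverse once the missing patients are added.

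| Assumption for missing patients | Reversed |
|---|---|
| Worst case: L-PRF all leak, control none | 28.6% |
| L-PRF leak at 20% (control 5.7%) | 4.9% |
| L-PRF leak at 10% (control 5.7%) | 2.4% |
| L-PRF leak at the planned 5% (control 5.7%) | 1.2% |

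**The case against.** The strongest reply is that section 20c offers a forecast and does not claim that nothing will be missing, and that the forecast may prove nearly right. The endpoint is a leak needing revision or another intervention. Surgical, hospital and follow-up data come from electronic files (sections 18a and 19). Leakage is also assessed at 2 and 4 weeks, and digital follow-up has been possible since March 2020. A leak before drop-out would therefore be known, and a later one might be found in the records. This stands as a reason to expect few missing outcomes. It is incomplete, because the article does not say that records will be searched for lost patients, and withdrawal ends data collection.

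It can also be said that worst-case and tipping-point analyses commonly belong in an analysis plan that is not shown. That is fair, and their absence is not the point here. The point is that section 20c assigns the missing-data check to a comparison that cannot perform it.

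Some stronger readings are tempting but unsupported:

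- A reader might infer that the verdict generally turns on one or two patients. In the example one extra leak still passes at the 90% level, and reversal needs both missing L-PRF patients to leak in a result already near the margin. (At the 95% level named for reporting, 7/110 vs 6/108 gives −7.1, but which interval governs is a separate question.)
- A reader might treat all 8 spare patients as missing outcomes, 4 per arm. The worst-case reversal is then about 60–62%, but 8/220 = 3.6% exceeds the plan's own rate.
- A reader might infer that patients excluded during surgery go unfollowed, or that the ITT analysis is in fact complete-case. Section 11b does not say the former, and section 20c defines ITT as everyone randomised.

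**Conclusion.** The point holds for the two sentences in section 20c. The comparison of the three sets is not a check on missing outcomes, and the stated expectation is not reconciled with sections 14, 11b and 18b. This conclusion is a matter of definition and needs no assumption about rates.

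The numerical consequence is a bound, not a forecast: a shift from −5.1 to −7.2 points in the example, and about 29% of passing results reversed in the worst case. It assumes the planning rates, 2 missing per arm, the simple 90% interval and the most adverse outcomes. Under less adverse assumptions, up to a 20% leak rate among missing L-PRF patients, reversal is about 1% to 5%.

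**What to change.** - Delete or reword the two sentences in section 20c, so that the three analyses are described as a check on adherence and treatment received only.
- State that leak status at 3 months is sought for every randomised patient where consent allows, including from hospital records.
- Pre-specify two sensitivity analyses of the primary risk difference: a worst case (missing L-PRF counted as leak, missing control as no leak), and a tipping-point table giving the number of missing-patient leaks at which the conclusion changes, shown beside the number actually missing in each arm.

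These should be settled before allocation is released. The cost is a few sentences and one table, with no extra patients. The downside is that the result may have to be described as fragile.

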**Assessments**						
Medical history	X					
EQ-5D	X		X	X	X	X
VAS	X		X	X	X	X
SNOT-22 questionnaire	X		X	X	X	X
SBI	X		X	X	X	X
MR imaging	X				X	X
Cost/material		X				
Intraoperative CSF leakage		X				
Nasal endoscopy to assess CSF leakage			X	X	X	X
Nasal endoscopy to assess wound healing			X	X	X	X
Nasal endoscopy to assess infection			X	X	X	X
Assessment of adverse events		X	X	X	X	X

*CSF *cerebrospinal fluid, *EQ-5D *EuroQol-5D, *SBI *Skull Base Inventory, *SNOT-22* Sino-Nasal Outcome Test with 22 items, *FU *follow-up, *VAS *visual analog scale

^a^2 weeks postoperative

^b^4 weeks postoperative

^c^3 months postoperative

^d^1 year postoperative

For the cost-effectiveness analysis, the “healthcare payer” perspective will be applied. This means that all direct treatment-related costs as well as costs related to the follow-up will be included in the analysis. In the cost analysis, the following elements will be considered: used materials during surgery (units), surgery duration (minutes), intensive care hospitalization time (days/hours), duration of hospitalization (days), associated facility and staff resources. These data will mainly be retrieved from the hospital records. The most recent unit prices at the time of analysis will be applied. Depending on the primary outcome, i.e., the effectiveness of sellar reconstruction, and the clinical effects of both treatments, either a cost-utility or a cost minimization analysis will be performed [10, 11]. In addition, the use of EQ-5D-3L to calculate QALYs at 6–12 weeks postoperative will be explored to compare EQ-5D utility scores to other outcomes described above.

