## Statistical methods

### Statistical methods for primary and secondary outcomes {20a}

Data will be analyzed in GraphPad Prism software using a simple *t*-test, or nonparametric Mann–Whitney *U* test when not normally distributed, with Bonferroni Holm correction for multiple testing. A *p*-value ˂0.05 is considered statistically significant. The primary outcome, i.e., CSF leakage, will be analyzed in terms of a difference in risk between the two treatment groups. The mean difference between the two treatment groups will be reported as a 95% confidence interval. Secondary endpoints are calculated using simple *t*-test, or nonparametric Mann–Whitney *U* test when not normally distributed, or Fisher’s exact test or chi-squared test, based on the number of events.

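### Filling missing cost-effectiveness values with the arm mean understates uncertainty in proportion to the missing share, and a results-dependent switch to cost minimisation can drop the uncertainty in effect

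*Protocol article*

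**What the plan says.** The Objectives {7} include showing that L-PRF is more cost-effective than commercial sealants. Four statements in the protocol article bear on that analysis.

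- **Missing data {20c}.** For the cost-effectiveness evaluation, labelled there as a secondary endpoint, "the predictive mean of the other values within the arm will be used". The same item says: "For the primary endpoint, no missing data are expected". So an imputation rule is written only for the economic data.
- **Type of analysis (Outcomes {12}, text after Table 2).** Depending on the primary outcome and the clinical effects of both treatments, "either a cost-utility or a cost minimization analysis will be performed".
- **QALYs (same paragraph).** As an addition, "the use of EQ-5D-3L to calculate QALYs at 6–12 weeks postoperative will be explored". Table 2 schedules EQ-5D at baseline, 2 weeks, 4 weeks, 3 months and 1 year.
- **Tests {20a}.** "Secondary endpoints are calculated using simple *t*-test, or nonparametric Mann–Whitney *U* test when not normally distributed". Costs are not named there.

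The only figure on missingness is in Sample size {14}: an "expected drop-out rate less than 2" per cent, given for the primary comparison. No rate is stated for EQ-5D or cost items.

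**The concern.** Putting the arm mean in place of each gap leaves the estimated mean where the observed patients put it, but adds artificial patients with no spread. The analysis then reports more precision than the data hold, so intervals are too short and nominal p-values too small. This bears on a stated objective of the trial.

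The choice of economic analysis is a separate matter. Cost minimisation treats the two arms as equally effective and compares costs only. A non-inferiority result excludes a loss of 7 points or more; it does not show a loss of zero. If cost minimisation replaces the cost-utility analysis after a favourable primary result, the remaining uncertainty in effect disappears from the economic conclusion.

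**Working it through.** **1. The plan's own figure.** Inputs from Sample size {14}: "The assumed success rate is 94.3% in the control arm"; 95% success assumed for L-PRF; margin 0.07; power 80% at a one-sided alpha of 0.05.

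n per arm = (1.645 + 0.842)² × (0.943×0.057 + 0.95×0.05) / (0.95 − 0.943 + 0.07)² = 6.18 × 0.10125 / 0.005929 ≈ 105.6, so 106 per arm and 212 in total, as stated. Allowing 2% drop-out, 212/0.98 gives 217, which the planned 220 covers. No stated figure is wrong. The article states no precision for the economic analysis.

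**2. Effect of arm-mean imputation.** Let an arm have n patients, n_obs of them observed, with observed variance s². Imputing the observed mean leaves the mean and the sum of squares (n_obs − 1)s² unchanged. The reported variance of the mean is (n_obs − 1)s² / [n(n − 1)]; the valid one is s²/n_obs. Hence

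SE reported / SE valid = √[n_obs(n_obs − 1) / (n(n − 1))] ≈ 1 − m, for missing share m.

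True two-sided type I error of a nominal 5% test = 2Φ(−1.96 × ratio). With n = 110 per arm:

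| Missing share | n_obs | SE ratio | Coverage of nominal 95% CI | Type I error |
|---|---|---|---|---|
| 2% (document's drop-out figure) | 108 | 0.982 | 94.6% | 5.4% |
| 5% (assumed) | 104 | 0.945 | 93.6% | 6.4% |
| 10% (assumed) | 99 | 0.900 | 92.2% | 7.8% |
| 20% (assumed) | 88 | 0.799 | 88.3% | 11.7% |

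Example at 10%: √[99×98 / (110×109)] = √(9702/11990) = 0.900.

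A simulation (8,000 runs per setting, normal and lognormal data, values missing completely at random) gave coverage of 94.0–94.7% at 2%, 91.8–92.0% at 10% and 88.1–88.7% at 20%. Complete-case analysis of the same data gave 94.5–95.4%.

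**3. Cost minimisation against the margin.** The assumed control failure rate is 100 − 94.3 = 5.7%. The margin puts the limit at 5.7 + 7 = 12.7%, more than twice that rate. Differences short of the limit remain compatible with a positive trial.

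**4. QALY window against visits.** With the visit windows in item {18b}, the 4-week visit falls in weeks 3–5 and the 3-month visit (12 weeks in the Fig. 2 legend) in weeks 10–14. Only the 3-month visit touches weeks 6–12, and its target date is the upper edge. At most 6/52 = 0.115 QALY can accrue within that window.

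**5. Rank test and mean cost.** This illustration assumes lognormal costs with log-SD 0.3 in one arm and 0.8 in the other, 110 per arm and 3,000 runs. With equal medians and a 32% higher mean, Mann–Whitney rejected in 6.7% of runs and Welch's t-test in 80%. With equal means, Mann–Whitney rejected in 89% and Welch's in 5.8%. The rank test therefore does not answer the question about mean cost.

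**The case against.** Much can be said for the plan.

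- **Size.** At the only figure the document gives, the effect is negligible (5.4% instead of 5%), and that allowance is meant to cover missing follow-up information. Costs come mainly from hospital records, where large gaps are unlikely. This stands as a limit on size. It does not settle the matter for EQ-5D: the drop-out figure was set for the primary comparison, whereas EQ-5D is a paper questionnaire due at four follow-up visits up to 1 year.
- **Wording.** The term used in {20c} could be loose language for a model-based prediction or for predictive mean matching. That is possible, so one cannot say for certain that patient characteristics would be ignored. The plain reading remains a mean of the other values in the arm, and the text needs correcting or clarifying either way.
- **Choice of analysis.** The choice is announced in advance and depends on clinical effects as well as the primary outcome. A reader might infer that meeting the margin alone triggers cost minimisation; the document does not say so. What stands is that the results decide, and that one of the two options omits the uncertainty in effect.
- **QALYs.** A reader might infer that the 1-year EQ-5D value goes unused. The document does not support this: the 6–12-week sentence describes an exploratory addition, and Outcomes {12} provides for comparisons with baseline over visits up to 1 year. Only the mismatch of window and visits stands.
- **Rank tests.** A reader might infer that costs will be tested by Mann–Whitney. This follows only by joining the general rule in {20a} to the label in {20c}, and only if costs are non-normal. It is an ambiguity to close, not a stated plan.

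**Conclusion.** The concern holds for two stated rules. First, the imputation rule in {20c}, read literally, understates the standard error by about the missing share. The consequence is negligible at 2% missing, modest at 5–10% (type I error 6.4–7.8%) and material at 20% (11.7%). These figures assume 110 per arm, values missing completely at random, a similar missing share in both arms and a normal approximation. Shares above 2% are assumptions. A flat statement that the intervals are too short to a material degree would go too far, because the document gives no missing rate for economic data and specifies no test or interval for the cost-effectiveness result.

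Second, letting the results choose between cost-utility and cost minimisation is unsound where the second would stand alone, since a 7-point margin does not show equal effect.

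The QALY window and the comparison of costs are secondary points of clarification. None of this touches the primary endpoint or the sample size. The changes should be made, but the trial's main conclusion does not depend on them.

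**What to change.** 1. In {20c}, replace the rule with multiple imputation by arm, using baseline data and the observed cost and utility values.
2. In Outcomes {12}, always report the cost-utility analysis with the uncertainty in effect, and show cost minimisation only as a secondary view.
3. Align the exploratory QALY window with the EQ-5D visits, for example as area under the curve from baseline to 3 months or to 1 year. Before choosing 1 year, confirm that costs are captured that long: Table 2 marks the cost and material item only at Visit 2, although the text says follow-up costs will be included.
4. State that costs are compared by difference in means, for example with bootstrap intervals, so that the general Mann–Whitney rule in {20a} does not apply to them.
5. If QALYs are adjusted for baseline utility, add an explicit exception to {20b}, which rules out adjusted analyses.

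**Cost.** More programming and wider intervals. If imputation recovers no information, the widening relative to the written rule is about 1/0.982 = 1.02 at 2% missing, 1/0.900 = 1.11 at 10% and 1/0.799 = 1.25 at 20%. EQ-5D needs no extra visit. Follow-up costs need no new data only if hospital records cover the chosen period. The article describes the trial as still recruiting, so on that footing the change can be made before analysis.
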